### Postoperative follow-up data recording

Follow-up will be conducted on day 3, at weeks 1, 2, 4, and 6, and at months 3 and 6 by an experienced research member blinded to the study. All the participants will complete a 6 months’ follow-up. The postoperative follow-up data recording parameters will also include VAS and PSS.

World Health Organization Quality of Life-BREF (WHOQOL-BREF) scores will be used to obtain scores for four domains related to quality of life: physical health (7 items), psychological (6 items), social relationships (3 items), and environment (8 items). This assessment will also include two stand-alone questions on overall quality of life and satisfaction with health. Each question will be rated on a scale of 1–5, with higher scores signifying better quality of life.

Functional disability will be assessed preoperatively and at 4 and 6 weeks and 3 and 6 months after surgery using the ODI. The ODI includes 10 questions about pain and activities of daily living. Each item has five response categories, ranging from no pain-related disability (0), to the worst possible pain-related disability (100).

The Patient and Observer Scar Assessment Scale (POSAS), comprised of subjective symptoms of pain and pruritus, will be assessed at 6 months postoperatively.

AEs such as nausea, vomiting, and steroid-related adverse effects (gastrointestinal bleeding, gastritis, delayed wound healing, etc.) will be documented for comparison of outcome.

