### Outcomes {12}

Clinical and demographic characteristics such as gender, age, weight, BMI, ASA status, type of surgery (laminoplasty or laminectomy), level of spine to be treated (cervical, thoracic, lumbar, or sacral), number of levels to be treated (1, 2, 3, 4 levels or more than 4 levels), and Oswestry Disability Index (ODI) will be recorded. After the operation, the duration of surgery, length of incision (in millimeters), and volume of local anesthesia (in milliliters) injected for preeemptive infiltration will be recorded. Postoperative complications such as postoperative pain due to spinal cord or nerve injury, wound infection, wound hematoma, delirium, serious adverse effects, and death may affect the follow-up process. Other complications such as allergic reaction, local or systemic toxicity, changes in wound healing, or increased wound drainage will be closely monitored.

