### Participant timeline {13}

The enrollment, interventions, assessments, and study visits of the PRE-EASE trial are presented in Table 1.

**Table 1 Tab1:** Study visits of the PRE-EASE trial

	Study period															
	Enrollment	Allocation	Post-allocation													
Time points	Preoperative	0 day (d)	Surgery	2 h	4 h	8 h	1 d	2d	3d	1 week (w)	Discharged	2w	4w	6w	3 months (m)	6 m
Enrollment																
Eligibility screening	X															
Informed consent	X															
Random allocation		X														
Interventions																
Betamethasone plus ropivacaine		X														
Ropivacaine		X														
Assessments																
Baseline data	X	X	X													
Intraoperative data			X													
Cumulative butorphanol consumption					X	X	X	X								
Patients with no butorphanol								X								
Total PCA button press count								X								
Time of first analgesia demand					X	X	X	X								
VAS_M_				X	X	X	X	X	X	X		X	X	X	X	X
VAS_R_				X	X	X	X	X	X	X		X	X	X	X	X
PSS				X	X	X	X	X	X	X		X	X	X	X	X
PONV				X	X	X	X	X								
RSS				X	X	X	X	X								
WHOQOL-BREF	X															X
ODI	X												X	X	X	X
POSAS																X
AEs																
Nausea				X	X	X	X									
Vomiting				X	X	X	X									
Gastritis				X	X	X	X									
GI bleeding				X	X	X	X									
Delayed wound healing				X	X	X	X									

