### Data collection and management

#### Plans for assessment and collection of outcomes {18a}

The primary outcome of interest will be recorded by an electronic memory system, which will include both valid and invalid presses for butorphanol demand in the 48-h postoperative period. The online recording system of the PCA demand will only be accessible to the sub-investigators blinded to the study. Secondary outcomes will be postoperative patient-reported scores, collected by a group of blinded research members in charge of the postoperative pain evaluation. At completion of the 6 months’ follow-up data collection, we will perform a data quality audit. An investigator will sample every participant file and check for missing data.

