#### Plans to promote participant retention and complete follow-up {18b}

Follow-up will be conducted on day 3, at weeks 1, 2, 4, and 6, and at months 3 and 6 by an experienced research member blinded to the study. All the participants will complete a 6 months’ follow-up. Follow-up data collection will either be done in person during the patient follow-up visits or by contact via telephone. Any participants who do not complete the entire 6 months’ follow-up process due to deviation from intervention, discontinuation for personal reasons, or failure of contact will not be replaced by other patients. Participants will be allowed to withdraw their consent or discontinue participation without any restriction at any time throughout the study, and further data associated with the trial will be collected.

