## Discussion

This trial will be a PROBE study. It will have better application in routine clinical practice, along with the clinical outcomes of a large simple research, which will permit a broader patient population and will include the advantage of randomization and an extensive evaluation of endpoints by blinded experts [19]. To our knowledge, there has been no attempt in the past to infiltrate laminoplasty or laminectomy with a preemptive local administration of betamethasone and ropivacaine. This study will add significant new knowledge to the effect and feasibility of preemptive wound infiltration of betamethasone.

Due to its large particles occluding the blood vessels supplying the spinal cord, betamethasone was previously reported to result in infarction of spinal cord after epidural analgesia [20]. However, we speculate that local peri-incisional infiltration of betamethasone is safe, as betamethasone has previously been used for intralesional [21], local infiltration [22], intramuscular [23], and intra-articular injections [16]. Local infiltration of steroid hormones will undeniably present the risk of delayed wound healing or local infection. However, we intend to use the lowest possible concentration of betamethasone for local infiltration based on the previous literature [15, 16, 22, 24], and thus this concentration should be considered safe. Wound healing and infection will be closely observed. The study will be immediately terminated in case of serious adverse reactions by the PRE-EASE Trial Management Group.

There are still some limitations regarding our study. Firstly, this is a single-center study; a multicenter study would be helpful in providing more significant data. In addition to incisional pain, acute pain after laminoplasty or laminectomy may be followed by long-term chronic pain that may not only originate from the incisional wound, but may also include neuropathic pain from spinal cord damage and nerve root injury. Another possible limitation of this study is that it will only involve infiltration of the surrounding tissue of the incision site. Therefore, we would like to suggest a further detailed study, regarding whether local betamethasone injection into the affected nerve roots before closure could be beneficial for postoperative pain after laminoplasty or laminectomy.

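### The outcome labelled wound healing is a single 6-month POSAS, described only as pain and itch and collectable by telephone, so it cannot support a statement about wound healing

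*Protocol article*

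**What the plan says.** Four parts of the protocol article bear on this outcome.

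- **Secondary outcomes** lists wound healing as an outcome, with POSAS at 6 months as its only measure. Table 1 agrees: POSAS is marked once, in the 6-month column.
- **Postoperative follow-up data recording** describes the instrument: "The Patient and Observer Scar Assessment Scale (POSAS), comprised of subjective symptoms of pain and pruritus, will be assessed at 6 months postoperatively".
- **Plans to promote participant retention and complete follow-up {18b}** sets the mode of contact: "Follow-up data collection will either be done in person during the patient follow-up visits or by contact via telephone". No outcome is exempted.
- **Plans for assessment and collection of outcomes {18a}** describes the source of the data: "Secondary outcomes will be postoperative patient-reported scores, collected by a group of blinded research members in charge of the postoperative pain evaluation". Data management {19} repeats this.

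Wound healing also appears outside this outcome. Outcomes {12} says that "changes in wound healing, or increased wound drainage will be closely monitored". The follow-up section says that "steroid-related adverse effects (gastrointestinal bleeding, gastritis, delayed wound healing, etc.) will be documented for comparison of outcome". The Discussion says: "Wound healing and infection will be closely observed". In Table 1 the row "Delayed wound healing" is marked at 2 h, 4 h, 8 h and 1 day.

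**The concern.** The label and the content of the outcome do not match. Pain and itch in a scar at 6 months are symptoms that the patient feels. They do not show whether the wound closed late, drained or became infected in the weeks after surgery. The scale is named for a patient and an observer, yet the text neither describes an observer part nor requires a form of contact in which an observer could see the scar.

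The Discussion itself names delayed healing and local infection as risks of infiltrating a steroid, and the Objectives hypothesise benefit without significant risks. If the two groups have similar 6-month POSAS scores, the natural report under the present label is that wound healing did not differ. The data would not support that statement.

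**Working it through.** The point involves no arithmetic, and the plan gives no figure for it to reproduce. The check is whether the sections can be read together consistently.

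**Step 1. Take the description of POSAS literally.** The outcome is then patient-reported pain and pruritus. A telephone call collects all of it, so {18b} causes no loss, and it fits the patient-reported description in {18a}. It does not fit Secondary outcomes, because symptoms at 6 months do not measure healing. It also leaves out the observer that the scale's name contains.

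**Step 2. Assume the full Patient and Observer scale is meant.** The description in the follow-up section is then incomplete, and {18a} and {19} describe this outcome wrongly. {18b} also allows a mode of contact in which an observer cannot rate a scar. Patients reached only by telephone would have the Patient scale alone, and a combined score would not be comparable with that of patients seen in person.

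**Step 3. Compare the two readings.** Each leaves at least one section in need of correction. They should not be added together: the mislabelling as pain and itch belongs to the first reading, and the missing observer part belongs to the second. On both, the text permits a completed outcome without any observer rating. On both, a single assessment at 6 months describes the scar and not the course of healing.

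**Step 4. Ask whether the other wound data repair the outcome.**

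| Section | What is promised | Times given |
|---|---|---|
| Outcomes {12} | "changes in wound healing, or increased wound drainage will be closely monitored" | none |
| Postoperative follow-up data recording | "steroid-related adverse effects (gastrointestinal bleeding, gastritis, delayed wound healing, etc.) will be documented for comparison of outcome" | none specific to this item |
| Discussion | "Wound healing and infection will be closely observed" | none |
| Table 1, row "Delayed wound healing" | adverse-event assessment | 2 h, 4 h, 8 h, 1 day |

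The only scheduled times end one day after surgery, too early to judge delayed healing. After that day, the only scheduled assessment in Table 1 that concerns the wound is the 6-month POSAS.

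**Step 5. Size.** The document gives no share of month-6 contacts made by telephone. The number of patients without an observer rating could be anything from none to all of those followed up, and nothing in the text narrows that range.

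**The case against.** The strongest reply is that this is loose wording in one secondary outcome of a condensed article. Much of that reply stands.

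- **The trial does collect other wound data.** A reader might infer that nobody is required to look at the wound at all. The documents do not support that. Wound infection, hematoma, changes in healing and drainage are listed as complications, delayed healing is to be documented as an adverse event, and Statistical methods {20a} compares adverse-event incidence between groups. The limitation is the schedule in Table 1, not an absence of monitoring.
- **The patient-reported description is weak evidence.** "Secondary outcomes will be postoperative patient-reported scores" cannot be literally true of the whole list, which includes pump-recorded butorphanol doses, press counts and the Ramsay scale. It does not prove that the observer part was dropped.
- **The telephone rule is general.** In-person contact is equally allowed, so an observer rating is possible; it is just not required. An operations manual and forms are mentioned and may settle who completes what. They would still not reconcile the label, the description and the contact rule in this text.
- **Size and selectivity of the loss.** A reader might infer that a large share of patients would lack the observer part, or that patients with wound problems would attend in person more often. Neither is documented.
- **Blinding.** A reader might see a special defect in pain and itch being reported by participants who are not on the blinded list. That applies to every patient-reported outcome in this openly declared open-label design. The follow-up assessor is blinded.

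**Conclusion.** The point holds in a limited form. An outcome presented as wound healing is described as subjective pain and pruritus, is measured once at 6 months, and can be completed by telephone without the observer rating that the scale's name implies. It cannot support a statement about wound healing. The adverse-event and complication monitoring is real but does not repair the outcome, because its scheduled assessments stop at 1 day.

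This rests on the text alone and needs no assumption about how many patients are telephoned. The loss of comparability between telephone and in-person patients arises only if the observer part is intended. The primary outcome, its analysis and the total of 116 patients are unaffected. The change should be made because the outcome concerns a risk that the protocol itself raises, but it does not threaten the trial's main result.

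**What to change.** 1. In Postoperative follow-up data recording and in Secondary outcomes, state that both the Patient and the Observer scales of POSAS are completed and reported separately, with the Observer scale rated by the blinded follow-up assessor already in the plan.
2. In {18b}, require the month-6 Observer rating to be made in person. Report patients reached only by telephone as having the Patient scale only, with their number in each group.
3. Rename the outcome scar quality at 6 months, and draw any conclusion on wound healing from the adverse-event and complication data.
4. For those data to carry that conclusion, reconcile the times marked in Table 1 for delayed wound healing with the sections that promise observation during follow-up.

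Most of this is wording. The real cost is a month-6 visit for patients who would otherwise have been telephoned; the document does not allow their number to be estimated. The assessor is already provided, although the text does not say whether this person is trained to rate scars, so some training may be needed. The sample size does not change.

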### Primary outcome

The primary outcome will be the cumulative butorphanol dose during the 48 h after surgery via the PCA device.

### Secondary outcomes

The secondary outcomes are as follows:
VAS_M_ and VAS_R_ 2 h, 4 h, 8 h, 24 h, 48 h, 72 h, 1 week, 2 weeks, 4 weeks, 6 weeks, 3 months, and 6 months after surgeryCumulative butorphanol dose for four separate periods (0–4, 4–8, 8–24, and 24–48 h), a total press count including both valid and invalid presses, first analgesia demand on the PCA devicePSS 2 h, 4 h, 8 h, 24 h, 48 h, 72 h, 1 week, 2 weeks, 4 weeks, 6 weeks, 3 months, and 6 months postoperativelyPONV and RSS scores 2 h, 4 h, 8 h, 24 h, and 48 h after surgeryWHOQOL-BREF scores preoperatively and 6 months postoperativelyFunctional disability assessed by ODI scores preoperatively and at 4 weeks, 6 weeks, 3 months, and 6 months after surgeryWound healing situation assessed by the POSAS scores at 6 months postoperatively.

### Participant timeline {13}

The enrollment, interventions, assessments, and study visits of the PRE-EASE trial are presented in Table 1.

**Table 1 Tab1:** Study visits of the PRE-EASE trial

	Study period															
	Enrollment	Allocation	Post-allocation													
Time points	Preoperative	0 day (d)	Surgery	2 h	4 h	8 h	1 d	2d	3d	1 week (w)	Discharged	2w	4w	6w	3 months (m)	6 m
Enrollment																
Eligibility screening	X															
Informed consent	X															
Random allocation		X														
Interventions																
Betamethasone plus ropivacaine		X														
Ropivacaine		X														
Assessments																
Baseline data	X	X	X													
Intraoperative data			X													
Cumulative butorphanol consumption					X	X	X	X								
Patients with no butorphanol								X								
Total PCA button press count								X								
Time of first analgesia demand					X	X	X	X								
VAS_M_				X	X	X	X	X	X	X		X	X	X	X	X
VAS_R_				X	X	X	X	X	X	X		X	X	X	X	X
PSS				X	X	X	X	X	X	X		X	X	X	X	X
PONV				X	X	X	X	X								
RSS				X	X	X	X	X								
WHOQOL-BREF	X															X
ODI	X												X	X	X	X
POSAS																X
AEs																
Nausea				X	X	X	X									
Vomiting				X	X	X	X									
Gastritis				X	X	X	X									
GI bleeding				X	X	X	X									
Delayed wound healing				X	X	X	X									

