### Objectives {7}

We hypothesize that preemptive local infiltration of betamethasone plus ropivacaine helps relieve postoperative pain, reduces the request for postoperative analgesics, and promotes early rehabilitation without significant risks.

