### Criteria for discontinuing or modifying allocated interventions {11b}

A detailed recording of all adverse events (AEs) throughout the course of the study will be properly recorded, closely monitored, and reported to the ethics committee as soon as possible, with the intentions of a resolution or stabilization, or even termination of the study if necessary.

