### Provisions for post-trial care {30}

There is no anticipated harm and compensation for trial participation.

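### Table 1 schedules the adverse-event checks only up to day 1, contradicting the text's study-long recording and leaving later steroid harms without a uniform assessment

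*Protocol article*

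**What the plan says.** Table 1, under Participant timeline {13}, has five adverse-event rows: nausea, vomiting, gastritis, GI bleeding and "Delayed wound healing". Each is marked at 2 h, 4 h, 8 h and 1 d, and nowhere later.

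The text describes a wider window:

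- Section {11b}, on stopping or changing the assigned treatment, states: "A detailed recording of all adverse events (AEs) throughout the course of the study will be properly recorded, closely monitored".
- Postoperative follow-up data recording, the section that covers day 3 to month 6: "steroid-related adverse effects (gastrointestinal bleeding, gastritis, delayed wound healing, etc.) will be documented for comparison of outcome".
- Outcomes {12} names wound infection and wound hematoma as complications and adds that "changes in wound healing, or increased wound drainage will be closely monitored".
- Discussion: "Local infiltration of steroid hormones will undeniably present the risk of delayed wound healing or local infection", and later "Wound healing and infection will be closely observed".

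Safety is part of the hypothesis. Objectives {7} expects that the treatment "promotes early rehabilitation without significant risks". Statistical methods {20a} plans a chi-square or Fisher's exact test on the incidence of adverse events.

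**The concern.** The table is what site staff work from when they decide what to ask at each visit. As printed, it asks about delayed healing only in the first 24 hours after closure, when a delay cannot yet be judged. From 48 h onward it asks about no adverse event at all. Wound infection, hematoma and drainage, all named in the text, have no row.

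This fits poorly with the trial's own rationale. The Background section chooses betamethasone because it is long-acting and stays partly in particulate form as a local depot. Harms from a prolonged local effect would be expected to show over days and weeks.

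At stake is the safety comparison. Without scheduled questions, late events reach the database only if a patient or clinician volunteers them. Only the postoperative pain evaluators, outcome assessors and data analysts are blinded ({17a}, {17b}). Patients and surgeons may know the allocation, so volunteered reports could differ between arms for reasons other than true incidence. A low count would then be hard to interpret in either direction.

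**Working it through.** **Step 1: is the table read correctly?** The text was extracted from PDF, so the column positions were checked first. The header row and the delayed-healing row each split into 17 cells, and the four marks fall under 2 h, 4 h, 8 h and 1 d. Other rows of the same table were then compared with Secondary outcomes:

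| Row in Table 1 | Marks in Table 1 | Times in the text | Agree? |
|---|---|---|---|
| VAS (movement, rest), PSS | 12, from 2 h to 6 months | the same 12 | yes |
| PONV, RSS | 5, from 2 h to 2 d | 2, 4, 8, 24 and 48 h | yes |
| ODI | preoperative, 4 and 6 weeks, 3 and 6 months | the same | yes |
| WHOQOL-BREF | preoperative, 6 months | the same | yes |
| POSAS | 6 months | the same | yes |
| Five adverse-event rows | 4: 2 h, 4 h, 8 h, 1 d | throughout the study; under the day-3 to month-6 follow-up | no |

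The alignment is sound, and among these rows only the adverse-event rows disagree with the text.

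**Step 2: how much follow-up has no scheduled check?** Postoperative assessment times, from the VAS row: 12. Times with an adverse-event mark: 4. Times without: 12 − 4 = 8. These eight are the 48-h visit and the seven follow-up contacts (day 3; weeks 1, 2, 4 and 6; months 3 and 6).

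**Step 3: do other instruments cover the gap?**

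- *PONV* runs to 48 h and grades both nausea and vomiting. Ending those two adverse-event rows at day 1 therefore loses nothing within the first 48 h.
- *POSAS* is done once, at 6 months. Secondary outcomes presents it as the wound-healing measure, while Postoperative follow-up data recording describes it through pain and pruritus. One assessment at 6 months cannot show an infection or a delay in healing that has since resolved, and it says nothing about gastritis or GI bleeding.

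No structured measure therefore covers the wound between day 1 and month 6, and none covers the GI harms after day 1.

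**Step 4: what could complete data show?** The documents give no adverse-event rates, so this is for scale only. If zero events are seen in n patients, the one-sided 95% upper limit is 1 − 0.05^(1/n).

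- n = 58 (one full arm): 1 − 0.05^(1/58) = 5.0%.
- n = 46 (58 × 0.8 = 46.4 after the planned 20% dropout): 1 − 0.05^(1/46) = 6.3%.

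For assumed true rates, the power with 58 per arm is about 17% for 5% versus 10%, 43% for 5% versus 15%, and 69% for 5% versus 20%. Even complete ascertainment would exclude only fairly large harms. That limit comes from the trial's size and is separate from the schedule.

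**The case against.** The strongest reply is that the text, read as a whole, already commits to longer capture. Beyond the sections quoted above, Adverse event reporting and harms {22} has any adverse event recorded, and the Data Monitoring Committee reviews safety at 25%, 50%, 75% and 100% of inclusions. On that view the table is an incomplete summary, and visit forms outside the article may hold the detailed checklist.

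Much of this stands. A reader might infer from the table that steroid harms lie wholly outside the assessment window and that the safety part of the hypothesis cannot be tested. The documents do not support that, because the text plainly intends wider recording and POSAS gives a structured, if late, wound outcome. Nor can one predict near-zero counts in both arms: no event rates are given, nausea and vomiting are on the list, and late events could still be volunteered.

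Three further inferences should also be dropped:

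- The Discharged column of Table 1 carries no mark for any assessment, so it is not an existing visit that lacks an adverse-event check.
- The sentence "There is no anticipated harm and compensation for trial participation" sits awkwardly beside the risk conceded in the Discussion, but it concerns post-trial care and has no bearing on how events are ascertained.
- A timeline table need not list every complication, so missing rows for infection, hematoma and drainage would be minor on their own.

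What the reply does not remove is the contradiction. The table sets explicit times for these named events, and those times conflict with text printed in the same article. A document that is not shown cannot settle which of the two staff will follow. The Data Monitoring Committee, too, can review only what has been collected.

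**Conclusion.** The point holds as an internal contradiction with a practical consequence. Table 1 stops the adverse-event checks at day 1, the text extends them through follow-up, and the collection window is left unclear. If the table is followed, 8 of 12 postoperative assessment times carry no adverse-event check, delayed healing is assessed only when it cannot be judged, and the incidence comparison in {20a} rests on day-1 data plus unsolicited reports.

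This rests on two assumptions: that staff may work from the printed schedule, and that a delay in healing is not recognisable within 24 hours of closure. The size of any resulting bias cannot be given, because the documents state no event rates.

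The sample size of 116, the primary outcome and its analysis are unaffected. The matter should be settled before recruitment, because uniform late data cannot be recovered once patients have passed those contacts.

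**What to change.** Reconcile Table 1 with {11b}, Outcomes {12}, Postoperative follow-up data recording and the Discussion:

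1. State the adverse-event collection window once, and use it in both table and text.
2. Extend the gastritis, GI bleeding and delayed-wound-healing rows to the 48-h visit, day 3, weeks 1, 2, 4 and 6, and months 3 and 6.
3. Schedule wound infection, hematoma and drainage, already named in the text, at the same times.
4. Have the blinded assessor ask these items in the same words in both arms. Contacts may be in person or by telephone ({18b}), so record which it was.
5. In {20a}, specify that the incidence of these events is compared by arm over the whole follow-up.

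The cost is a few extra questions at eight contacts that already take place. No new visit, no added patients and no change to the primary analysis are needed.
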